### Hypotheses

We hypothesize that access to BWW will increase mental health recovery orientation and reduce symptoms of depression and anxiety among patients seeking specialized mental health care. Further, we expect that a greater response to BWW will be predicted by higher baseline belief in credibility and outcome expectancy of the intervention as well as actual level of engagement with the intervention. The core mechanisms by which we hypothesize BWW to be effective include: 1) enhanced self-efficacy to self-manage mental health conditions through acquisition of knowledge, personal use of tracking tools, and vicarious learning; and 2) rapid access to peer and facilitated support within a constrained health care system leading to a feeling of security and enhanced ability to cope in crisis situations.

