#### Allocation and blinding

At enrollment, a 2:1 allocation ratio will be used to randomize participants to ITG or DTG. This allocation ratio was chosen to immediately provide the intervention to more participants and increase likelihood of participation. Participants and providers will not be blind to treatment group. Randomization sequences will be generated independently and will be stratified by site and recruitment setting. Allocation sequence will be concealed until after baseline data has been collected to blind those involved in recruiting and consenting procedures. Group allocation will be revealed by phone or email. At t = 3 months, ITG participants who opt in to the nested study arm, will be randomized 1:1 to a 3 month BWW extension (ITG-e) or no extension (ITG-n). Group allocation will again be revealed via phone or email. The nested treatment extension arm will be concealed from participants at enrollment to encourage maximal usage of the intervention during the first 3 months. All data analyses will be blinded.

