##### Baseline data

At time of consent, participants will complete a baseline questionnaire assessing socio-demographics, mental health history, measures of treatment credibility and outcome expectancy, and all outcome measures. Due to the length of time required to complete consent and all baseline questionnaires, baseline data may be collected in 1 of 3 ways depending on recruitment setting and participant preference: 1) by web survey (default); 2) by phone; or 3) in-person hard-copy.

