##### Baseline belief in treatment credibility and outcome expectancy

Participants are asked to rate their belief in the credibility of self-help resources to improve mental health with the author-generated statement: “Self-help tools including on-line services or books are helpful for people with mental health problems” on a 4-point scale from ‘definitely agree’ to ‘completely disagree.’ In addition, they will be asked about their outcome expectancy of BWW to improve their mental health. Item #4 from the Credibility and Expectancy Questionnaire [29] will be used, “After having access to BWW for 3 months, how much improvement in your mental health do you think will occur?” Participants are asked to rate their response from 0 to 100 % with options available in 10 % increments. This single item has been shown to correlate strongly with psychotherapy outcomes [30].

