##### Primary and secondary analyses

Baseline descriptive statistics will be generated overall, between treatment groups and between recruitment settings. Employment status and medication use will be described at baseline and 3 months. Prior 3-month health care utilization assessed with the CSRI (and validated with health administrative data when available) will be described at baseline and at 3 months. All primary and secondary outcomes will be described at baseline and 3 months, including the RAS-r and CIQ subscales. In addition, at baseline and 3 months, we will describe the proportion of participants with PHQ-9 and GAD-7 scores of 10 or more, indicative of clinically important levels of depression and anxiety [40], respectively. At 3 months, we will describe clinically important cutoffs on the PHQ-9 and GAD-7 including a reduction of 5 or more points from baseline (clinically meaningful change), reduction in score of 50 % or more from baseline (response), and a score less than 10 (remission) [40]. Adverse event descriptive data will be reported at 3 months, and again at 6 months for the BWW extension group. BWW satisfaction descriptive data will be reported at 3 months for ITG participants and 6 months for DTG participants.

The primary outcome, RAS-r at 3 months, will be analyzed with an intent-to-treat analysis using an ANCOVA controlling for baseline RAS-r score as well as treatment group, unadjusted and adjusted for baseline PHQ-9, baseline GAD-7, age, sex, education, relationship status, household income, duration of episode, and recruitment setting. In sensitivity analysis, we will repeat this using a marginal structural model to account for attrition.

The same analysis will be repeated for all secondary outcomes at 3 months controlling for baseline score and treatment group. Analysis of 3 month data will be completed after all 3 month data have been collected.

In the subset of ITG participants who opt in to the nested extension study, we will examine outcomes at 6 months between treatment groups. Analysis of primary and secondary outcomes will be repeated as described above, controlling for scores at both baseline and 3 months.

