##### Exploratory analyses

The first exploratory analysis will examine a subset of the ITG group who had a PHQ-9 or GAD-7 score of at least 10 at baseline. Participants will be categorized as ‘responders’ or ‘non-responders’ based on whether or not they achieved at least a 50 % reduction in the PHQ-9 or GAD-7 at 3 months relative to baseline. A logistic regression model will be built to predict whether or not they were a responder using age, gender, education, relationship status, household income, baseline belief in treatment credibility and outcome expectancy, and recruitment setting as predictors. We will also assess the contribution of BWW utilization, outpatient mental health visits, and medication changes during the intervention months as predictors of response.

Second, we will examine engagement with the BWW among ITG participants. The number of logins and total time on the site will be separately predicted with age, gender, education, relationship status, living situation, household income, baseline belief in treatment credibility and outcome expectancy, baseline PHQ-9 and GAD-7 scores, duration of current episode, recruitment setting and outpatient mental health visits.

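### The adjusted 3-month ANCOVA leaves out baseline outcome expectancy, already collected in both arms before allocation is revealed: a missed low-cost improvement, not an error

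*Protocol article*

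**What the plan says.** Under Primary and secondary analyses, the protocol article specifies an intent-to-treat ANCOVA of 3-month RAS-r on baseline RAS-r and treatment group, "unadjusted and adjusted for baseline PHQ-9, baseline GAD-7, age, sex, education, relationship status, household income, duration of episode, and recruitment setting". The same analysis is repeated for the secondary outcomes at 3 months. A marginal structural model for attrition is planned as a sensitivity analysis; the covariates of its weights are not listed.

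Under Baseline data, "participants will complete a baseline questionnaire assessing socio-demographics, mental health history, measures of treatment credibility and outcome expectancy, and all outcome measures". Under Allocation and blinding, "Allocation sequence will be concealed until after baseline data has been collected". The expectancy item asks "After having access to BWW for 3 months, how much improvement in your mental health do you think will occur", answered from 0 to 100 % in steps of 10. Of this item the article says: "This single item has been shown to correlate strongly with psychotherapy outcomes".

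The Hypotheses section expects that "a greater response to BWW will be predicted by higher baseline belief in credibility and outcome expectancy of the intervention". The item enters only the exploratory models, which are confined to the immediate treatment group (ITG). The responder model, for example, takes "baseline belief in treatment credibility and outcome expectancy, and recruitment setting as predictors".

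**The concern.** Expectancy meets the usual conditions for a baseline covariate. It is measured in the same way in both arms, it cannot be affected by allocation, and the authors themselves connect it with outcome. The adjusted model nevertheless takes in income and relationship status, for which the article makes no such claim, and leaves expectancy out.

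Two things could be at stake. One is precision: a covariate that predicts outcome beyond those already in the model narrows the interval. The other is attrition. The trial is unblinded, the control group (DTG) waits for access, and 30 % loss is assumed. If expectancy affects who answers at 3 months, and does so differently in the two arms, completers will differ in a variable that may predict outcome.

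**Working it through.** **Inputs from the article (Power calculation).** 700 analysed participants in a 2:1 ratio (466.7 and 233.3), alpha 0.05, power 0.9, correlation 0.8 between baseline and 3-month RAS-r, detectable difference 1.35. The SD is not given, and neither is any correlation of expectancy with RAS-r.

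**The plan's own figure.** Detectable difference = SD × √(1 − 0.8²) × (1.960 + 1.282) × √(1/233.3 + 1/466.7) = SD × 0.6 × 3.242 × 0.0802 = SD × 0.156. The figure of 1.35 cannot be reproduced independently without an SD. It corresponds to an SD of 1.35/0.156 ≈ 8.66 if two-sided (9.59 if one-sided). I use 8.66, which makes the residual SD 0.6 × 8.66 = 5.19.

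**Precision.** Let r_f and r_b be the assumed correlations of expectancy with 3-month and baseline RAS-r. The share of residual variance it explains is (r_f − 0.8 r_b)² / [0.36 (1 − r_b²)], and the SE is multiplied by √(1 − share).

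| r_f | r_b | share | SE reduction |
|---|---|---|---|
| 0.4 | 0.1 | 0.1024/0.3564 = 0.287 | 15.6 % |
| 0.3 | 0.2 | 0.0196/0.3456 = 0.057 | 2.9 % |
| 0.2 | 0.3 | 0.0016/0.3276 = 0.005 | 0.2 % |
| 0.24 | 0.3 | 0 | 0 % |

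Over r_f 0.2 to 0.4 and r_b 0.1 to 0.3 the reduction therefore runs from 0 to 15.6 %. The central case (0.3 and 0.2) is worth 700 × (1/0.9433 − 1) ≈ 42 completers. It lowers the detectable difference from 1.35 to 1.35 × 0.971 = 1.31. The formula ignores PHQ-9, GAD-7 and the other covariates, which may share variance with expectancy.

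**Attrition.** Take a true effect of zero, 70 % retention in each arm, and retention logistic in standardised expectancy. Write r_T and r_C for the partial correlation of expectancy with outcome in ITG and DTG, and m_T and m_C for mean expectancy among those retained. To a close approximation, bias without expectancy = 5.19 × (r_T m_T − r_C m_C). Here m = slope × mean of p(1 − p) / 0.7, where p is the retention probability. A slope of 0.5 gives m = 0.5 × 0.200/0.7 = 0.143; 0.8 gives 0.213; −0.3 gives −0.088.

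*Expectancy predicts outcome equally in both arms:*

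| partial r | slope ITG | slope DTG | bias without it | with it |
|---|---|---|---|---|
| 0.3 | 0.5 | 0.5 | about 0 | about 0 |
| 0.24 (central case) | 0.5 | 0 | 0.18 | about 0 |
| 0.24 | 0.8 | −0.3 | 0.37 | about 0 |
| 0.3 | 0.5 | 0 | 0.22 | about 0 |
| 0.3 | 0.5 | −0.5 | 0.44 | about 0 |

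Large-sample simulations agree to within about 0.02. At a partial r of 0.5, close to the top of the precision grid (√0.287 = 0.54), the last two rows become 0.38 and 0.74.

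*Expectancy predicts outcome in ITG only (partial r 0.3 there, 0 in DTG), simulated:*

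| slope ITG | slope DTG | bias without it | with a main-effect term |
|---|---|---|---|
| 0.5 | 0 | 0.22 | 0.07 |
| 0.5 | −0.5 | 0.22 | −0.08 |
| 0.5 | 0.5 | 0.22 | 0.22 |

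A main-effect term reduces this bias when the slopes differ but does not remove it. It does nothing when the slopes are equal, because completers then have the same mean expectancy in both arms.

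**The case against.** The strongest reply is that this is a preference. The model already holds baseline RAS-r, assumed to correlate 0.8 with follow-up, together with symptom scores and recruitment setting. Omitting a further covariate does not bias a randomised comparison with complete data. That stands, and it is why this is not called an error.

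A reader might infer that the plan drops an item it knows to be strongly prognostic for its primary outcome. The article does not say that. Its statement concerns psychotherapy outcomes, gives no coefficient and does not mention RAS-r. The item asks about benefit from BWW, which DTG does not receive before the primary endpoint. Expectancy may therefore act mainly within ITG, which fits the stated hypothesis and the ITG-only exploratory models. No such claim is made for the author-written credibility item.

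A reader might also infer that the plan leaves attrition bias uncontrolled. That does not follow either. The marginal structural model is planned, and its weights may already include expectancy in an analysis plan not shown. Dropout slopes that differ by arm are an assumption. Hopeful DTG participants have a reason to stay, so similar slopes are equally plausible. Follow-up is by survey and telephone, with no stated dependence on BWW use.

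What remains is narrower. The covariate list is stated, so the omission from the adjusted ANCOVA is a choice visible in this document. The marginal structural model is only a sensitivity analysis.

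**Conclusion.** The point holds as a recommended improvement to the adjusted 3-month analysis. The documents establish that expectancy is available in both arms before allocation is revealed, is described as related to outcome in psychotherapy, and is absent from the covariate list. They do not establish how much is lost.

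The precision gain is 0 to about 16 % of the SE under the assumed correlations, and about 3 % in the central case. Bias in the completer comparison requires that expectancy predicts outcome and that either dropout depends on it differently by arm or its effect on outcome differs by arm. The moderate scenarios give roughly 0.2 to 0.4 points, or 13 to 33 % of 1.35 (0.18/1.35 and 0.44/1.35), and stronger assumptions give more. With equal slopes and equal effects it is about zero. All figures in points scale with the back-solved SD of 8.66. If expectancy works only in ITG, a main-effect term is at best a partial remedy, which is a reason to use the item in the attrition weights as well.

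**What to change.** Add baseline outcome expectancy (0 to 100 %, as a linear term) to the pre-specified covariates of the adjusted 3-month ANCOVA for the primary and secondary outcomes. Name it among the covariates of the attrition weights in the marginal structural model, with its relation to retention allowed to differ by arm. Adding the credibility item, or extending the change to the 6-month extension model, is optional. The case there is weaker: the article makes no prognostic claim for the credibility item, and the extension model already conditions on 3-month scores.

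The cost is a line of text and one degree of freedom of about 700, with no new data. The article reports 475 participants consented against a target of 1000, and 3-month data are analysed only once all are collected. At that stage the change could still be pre-specified.

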##### Exploratory analyses

The first exploratory analysis will examine a subset of the ITG group who had a PHQ-9 or GAD-7 score of at least 10 at baseline. Participants will be categorized as ‘responders’ or ‘non-responders’ based on whether or not they achieved at least a 50 % reduction in the PHQ-9 or GAD-7 at 3 months relative to baseline. A logistic regression model will be built to predict whether or not they were a responder using age, gender, education, relationship status, household income, baseline belief in treatment credibility and outcome expectancy, and recruitment setting as predictors. We will also assess the contribution of BWW utilization, outpatient mental health visits, and medication changes during the intervention months as predictors of response.

Second, we will examine engagement with the BWW among ITG participants. The number of logins and total time on the site will be separately predicted with age, gender, education, relationship status, living situation, household income, baseline belief in treatment credibility and outcome expectancy, baseline PHQ-9 and GAD-7 scores, duration of current episode, recruitment setting and outpatient mental health visits.

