### Limitations

The requirements of health system stakeholders involved in this initiative necessitated a number of compromises in the design of this evaluation. First, the sample size requested by the funder necessitated broad inclusion criteria which is pragmatic but may present challenges around interpreting efficacy, particularly if no effect of the intervention is observed. We have limited recruitment to treatment settings where BWW is theorized to have the greatest applicability, and will seek to understand through our analysis and qualitative data if particular participant groups respond differently. Second, stakeholder desire for all participants to receive the intervention within a specific time interval meant that a control arm could not be continued throughout, and necessitated a short follow-up period, which will limit the interpretation of sustained intervention effectiveness. We have included a nested intervention extension arm open to interested participants to pragmatically evaluate the effectiveness of the sustained intervention in a self-selected patient group. Third, the specific intervention, BWW, was selected by the partners and although the process evaluation will seek to determine which components and mechanisms lead to the observed effects, it is uncertain how the findings of the study will be generalizable to other on-line mental health interventions.

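### The planned responder model uses the ITG alone, so it can show who improves while on BWW but cannot test the hypothesis about who responds to BWW

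*Protocol article*

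**What the plan says.** Under Hypotheses, the protocol article writes that "we expect that a greater response to BWW will be predicted by higher baseline belief in credibility and outcome expectancy of the intervention", and adds "as well as actual level of engagement with the intervention". Under Limitations, the authors say they "will seek to understand through our analysis and qualitative data if particular participant groups respond differently".

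The matching quantitative analysis is under Exploratory analyses: "The first exploratory analysis will examine a subset of the ITG group". The subset is limited to people at or above 10 on either symptom scale when they enrolled. A responder is someone with "at least a 50 % reduction in the PHQ-9 or GAD-7 at 3 months relative to baseline". A logistic model then predicts responder status from eight baseline items: age, gender, education, relationship status, household income, credibility, expectancy and recruitment setting. BWW utilization, outpatient visits and medication changes are examined as further predictors. The model has no DTG data, no treatment term and no interaction.

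The randomized comparison under Primary and secondary analyses estimates a main effect of treatment only. No effect-modification analysis appears elsewhere in the article.

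The baseline questionnaire, given to every participant, covers "measures of treatment credibility and outcome expectancy, and all outcome measures". Under Allocation and blinding, allocation stays concealed until baseline data are in. Table 1 schedules the PHQ-9, GAD-7 and RAS-r at 3 months, when, under Study design, the DTG is still the control group.

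**The concern.** A greater response to BWW is a statement about a contrast: how much better a person does with BWW than without it, and whether that gain rises with expectancy. A within-person 50% reduction is not such a contrast. ITG participants may also improve through usual care, through the natural course of an episode, or through regression to the mean after selection on a score of at least 10.

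The protocol itself gives reasons to expect prognostic effects without BWW. Usual care may include drug and non-drug treatment. The section on credibility and expectancy says the chosen expectancy item correlates strongly with psychotherapy outcomes, and psychotherapy services are among the recruitment settings. Expectancy could therefore predict improvement in the DTG as well.

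At stake is the reading of one stated hypothesis. A marker of good prognosis could be taken for a marker of benefit from BWW, or a true modifier could be hidden by an opposing prognostic effect.

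**Working it through.** **The plan's own figures.** The plan states no figure for the responder analysis. Its only design figure is the detectable RAS-r difference of 1.35. That equals (1.960 + 1.282) × SD × √(1 − 0.8²) × √(1/233.3 + 1/466.7) = 0.1559 × SD, which implies an SD of about 8.66 (two-sided). The SD is not given, so the figure cannot be verified, and nothing below depends on it. What carries over is the sample: 1000 × 0.7 = 700 completers, split 2:1 into about 467 ITG and 233 DTG.

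**What the model estimates.** Let x be the standardized predictor and T = 1 for ITG. In both arms,

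logit P(responder) = a + p·x + t·T + i·x·T,

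where p is the prognostic effect and i the modification of the BWW effect. Setting T = 1 gives (a + t) + (p + i)·x. The ITG-only slope is p + i. The DTG supplies p, and only with it can i be isolated. This is algebra and needs no assumed number.

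**Illustration.** The documents do not give the share of patients at or above the cutoff, the control response rate or the odds ratios. Assumed: share 60, 75 or 90% (280/140, 350/175 or 420/210 ITG/DTG), control response 15 or 25%, one predictor, no missing data, Wald tests at |z| > 1.96, and 1,500 simulated trials per setting. The Monte Carlo standard error at 5% is √(0.05 × 0.95/1500) = 0.6 percentage points.

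*Prognostic only, BWW without any effect (t = 0, i = 0).* Percentage of trials in which the term is significant:

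| Share at cutoff | Control response | OR 1.3: ITG-only | OR 1.3: interaction | OR 1.5: ITG-only | OR 1.5: interaction |
|---|---|---|---|---|---|
| 60% | 15% | 34.9 | 4.3 | 69.2 | 5.3 |
| 60% | 25% | 46.2 | 5.1 | 82.5 | 4.9 |
| 75% | 15% | 40.9 | 5.5 | 76.7 | 5.1 |
| 75% | 25% | 56.3 | 5.1 | 90.5 | 3.9 |
| 90% | 15% | 49.1 | 4.7 | 84.1 | 5.1 |
| 90% | 25% | 65.9 | 4.3 | 94.3 | 4.6 |

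The ITG-only model recovers the prognostic odds ratio (1.30–1.31 and 1.51–1.52), as the algebra predicts.

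*True modifier hidden by opposite prognosis (prognostic OR 0.67, interaction OR 1.5, treatment OR 1.5).* The ITG-only slope cancels to an odds ratio of about 1.00 and is significant in 4–6% of trials. The interaction test detects the modifier in 30–54%.

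*True modifier without prognostic effect (interaction OR 1.5, treatment OR 1.5).* The ITG-only model is significant in 77–98% of trials and the interaction test in 33–55%. The ITG-only model looks more powerful here only because p happens to be zero, which it cannot show.

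**The case against.** **The analysis is exploratory and coherent as a prediction model.** The article defines response as a 50% reduction, so predicting responder status is legitimate, and finding a real prognostic association is then no error. This stands. The percentages above show how often a result would be open to misreading as response to BWW, not how often the model fails as a predictor. The mismatch with the stated hypothesis remains, because no other quantitative analysis tests it.

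**The question of for whom BWW works has another home.** A reader might infer that the trial has no other means of addressing it. The documents do not support that. Evaluation framework assigns the question to the Realist Evaluation, and the qualitative Data analysis section gives a method for it. The gap is in the quantitative test only.

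**The control arm's baseline data are not idle.** A reader might infer that they go unused. In fact the adjusted ANCOVA uses age, sex, education, relationship status, income and recruitment setting in both arms. Credibility and expectancy are the predictors with no both-arm analysis.

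**Mistargeting is not established.** That a prognostic factor would be published as a guide to whom to offer BWW is conjecture about reporting.

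**The 50% cutoff is not an error.** It is a cited convention, and replacing it is a preference. Adding baseline severity to the responder model would be an improvement, not a correction.

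**The remedy has limits.** Interaction power is low. Participants rate their expectancy of BWW itself, and in an unblinded trial those with high hopes who are told to wait may do worse, so an expectancy interaction may partly reflect disappointment in the DTG. Engagement does not exist in the DTG before month 3, so an interaction cannot address that part of the hypothesis. A complier-average effect would not either: it estimates benefit among users, not whether more use goes with more benefit.

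**The detail may be left to the analysis plan.** In part. The article already fixes the population, outcome, model and predictors. If the plan, which is not shown here, adds a both-arm interaction, the point is met.

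**Conclusion.** The point holds in a limited form. The ITG-only model can describe who improves while on BWW. It cannot show that baseline credibility or expectancy predicts response to BWW, because it estimates p + i and the hypothesis concerns i. That conclusion rests on the model's structure alone. Its practical size (35–94% against 4–5% for a purely prognostic predictor, and 4–6% against 30–54% for a masked modifier) depends on the assumed cutoff share, response rate and odds ratios.

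The primary and secondary randomized comparisons are untouched, and the affected analysis is labelled exploratory. This is a worthwhile, inexpensive improvement that lets the trial test its own hypothesis. It is not a threat to the trial's main conclusions.

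**What to change.** - **Credibility and expectancy.** Fit 3-month models in ITG and DTG together with treatment, predictor, treatment-by-predictor, baseline score, and recruitment setting and site (the randomization strata). Name the outcomes in advance. Report the interaction as an estimate with a confidence interval.
- **Other baseline moderators.** Treat them as exploratory. Eight predictors by three outcomes (RAS-r, PHQ-9, GAD-7) would be 24 tests. If they were independent and all null, the chance of at least one result at 5% is 1 − 0.95²⁴ = 71%.
- **ITG-only model.** Keep it, labelled as predicting improvement while on BWW. Optionally add baseline PHQ-9 and GAD-7, as the article's own engagement model does.
- **Utilization.** Describe the results as associations only. Use of BWW follows randomization and may reflect motivation or early change in symptoms.
- **Caveats to state.** Interaction power on the responder outcome is roughly 30–55% for an interaction odds ratio of 1.5 per SD under the assumed inputs; power on continuous scores was not calculated. An expectancy interaction may partly reflect disappointment in the waiting arm.

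The cost is revised wording and a few more models. No new data, visits or participants are needed.

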### Participant eligibility

Eligible patients are individuals 16 years of age and older who are seeking mental health care at any of the participating sites. Inclusion criteria: 1) able to provide informed consent; 2) able to read in English; 3) able and willing to access the internet, 4) able to navigate an on-line program independently or with minimal assistance; and 5) have or are willing to obtain and use an email address. Exclusion criteria: There are no exclusion criteria but clinicians are reminded that BWW is a peer community and participants need to be able to coherently and respectfully interact with others. As such, we do not recommend individuals with severe psychosis or behavioural disorders be recruited.

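### The exploratory responder variable counts a halving of either PHQ-9 or GAD-7, even on a scale that was below 10 at baseline while the elevated scale did not improve.

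*Protocol article*

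**What the plan says.** All references are to the protocol article.

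- **Exploratory analyses, who enters:** "a subset of the ITG group who had a PHQ-9 or GAD-7 score of at least 10 at baseline". One elevated scale is enough.
- **Exploratory analyses, who responds:** a participant with at least a 50 % "reduction in the PHQ-9 or GAD-7 at 3 months relative to baseline". The second "or" is not linked to the first.
- **Exploratory analyses, use of the label:** "A logistic regression model will be built to predict whether or not they were a responder".
- **Primary and secondary analyses, cutoff:** the plan describes the proportions with "PHQ-9 and GAD-7 scores of 10 or more, indicative of clinically important levels of depression and anxiety", at baseline and at 3 months.
- **Primary and secondary analyses, 3-month descriptions:** these include a "reduction in score of 50 % or more from baseline (response") "and a score less than 10 (remission"). Neither carries a baseline condition, and no denominator is given.
- **Participant eligibility:** no minimum symptom score is set ("There are no exclusion criteria but clinicians are reminded that BWW is a peer community"), so people below 10 on one or both scales can be enrolled.

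**The concern.** The plan uses a score of 10 to decide who has symptoms worth tracking, then drops that threshold when it counts improvement. A participant can enter because of severe depression, stay just as depressed, and be called a responder because an already low anxiety score moved by a point or two. A small absolute change halves a low score, so scales below 10 are where retest noise most easily produces a response.

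The label is the outcome of the model that addresses a stated hypothesis: that credibility, expectancy and engagement predict response to the platform. If part of the responder group did not improve on the problem that brought them into the analysis, the model answers a blurred question. The remission wording has a related but smaller defect, since a person who was never at 10 cannot remit.

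**Working it through.** The plan states no response or remission rate, so there is no figure to reproduce. The check has a part that follows from the text and a part that rests on assumptions.

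**1. Direction for response (from the text).** Let A be the participants who halve a scale that was at or above 10 at baseline, and B those who halve either scale. Everyone in A is in B, so rate(B) ≥ rate(A) in any data. B exceeds A as soon as one participant halves only a scale that started below 10.

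**2. Direction for remission (from the text, with one mild condition).** Let p be the share at or above 10 on a scale at baseline, R the share of these below 10 at 3 months, and S the share of the others who are below 10 at 3 months. Over all participants the rate is p·R + (1 − p)·S. This exceeds R whenever S > R, that is, whenever people who start low are likelier to end low.

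**3. Size of the response excess (assumed inputs).** None of these inputs is in the protocol:
- PHQ-9 mean 13, SD 6; GAD-7 mean 11, SD 5.2
- cross-scale correlation 0.65
- baseline to 3-month correlation (retest) 0.5 to 0.8
- mean change 0, −2 or −4 on both scales
- normal scores, rounded and limited to 0–27 and 0–21

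Under these inputs about 80 % of participants enter the subset, and about a third of the subset is elevated on one scale only. The own-scale rule is a halving on any scale at or above 10 at baseline.

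| Mean change | Retest | Either scale (as written) | Own scale | Excess (points) | Responders on the low scale only |
|---|---|---|---|---|---|
| 0 | 0.5 | 18.3 % | 16.2 % | 2.1 | 11–12 % |
| 0 | 0.8 | 7.2 % | 4.6 % | 2.6 | 36 % |
| −2 | 0.5 | 32 % | 29 % | 3.4 | 11 % |
| −2 | 0.8 | 19 % | 14 % | 5.5 | 28–29 % |
| −4 | 0.5 | 49 % | 45 % | 4.5 | 9 % |
| −4 | 0.8 | 39 % | 31 % | 8.3 | 21 % |

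The last column is the excess divided by the rate as written; for the second row, 2.6 / 7.2 = 36 %.

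**4. Size for PHQ-9 remission, same inputs.** Here p = 0.72.
- No mean change, retest 0.8: R = 0.12 and S = 0.69. The rate over all is 0.72 × 0.12 + 0.28 × 0.69 = 0.086 + 0.193 ≈ 0.28. The share never at 10 is 0.193 / 0.28 ≈ 69 %.
- Mean change −4, retest 0.5: R = 0.44 and S = 0.776. The rate over all is 0.317 + 0.217 = 0.534. The share never at 10 is 0.217 / 0.534 ≈ 41 %.

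**5. Sensitivity to the assumptions.** A second set used PHQ-9 means 11 to 17, GAD-7 means 9 to 14, SDs 6 and 5, cross-scale correlation 0.5 to 0.7, retest 0.6, and mean falls of 0 to 4 (PHQ-9) and 0 to 3 (GAD-7). The response excess was about 0.6 to 9 points, with 6 to 24 % of responders qualifying only on the low scale. Of those below 10 at 3 months, 27 to 65 % (PHQ-9) and 36 to 73 % (GAD-7) had been below 10 at baseline. S > R held in every scenario.

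**The case against.** **Scope.** The responder model is labelled exploratory and lies within the immediate-treatment group, so no between-arm claim depends on it. In a sample of mixed diagnoses an either-scale composite can be defended, and a fall from 8 to 4 on the second scale is not obviously a false response. The scope limit stands. The defence of the composite does not rescue the rule, because it also admits a participant whose elevated scale is unchanged.

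**A linked reading.** One could read the text as judging each participant on the scale that qualified them. The text does not say so, and that reading would leave participants elevated on both scales without a rule.

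**Remission.** No denominator is stated, and the analysis plan, which is not at hand, may supply one. Over all participants, remission is simply the complement of the 3-month proportion at 10 or more, which the plan reports beside the baseline proportion. An attentive reader could see how many started low. This largely stands, and it is why remission is the lesser point.

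**Stronger readings to avoid.**
- A reader might infer that the definitions favour the platform. They do not: the remission definition is the same in both randomized arms.
- A reader might infer bias in every coefficient of the logistic model. The calculation contains no predictors, so misclassification of the outcome is shown but its effect on any coefficient is not.
- The 36 % share should not be quoted alone: it arises where only 7.2 % respond and the excess is 2.6 points.
- The descriptive response rate also lacks a baseline floor, but nothing shows that it must be inflated.

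**Conclusion.** The point holds for the responder variable. As written, it can only give a rate equal to or above the rate on the qualifying scale, and it misclassifies the dependent variable of the logistic model. That direction follows from the wording. The size rests entirely on the assumed distributions: about 2 to 8 percentage points, with 9 to 36 % of responders qualifying only on the low scale.

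For remission the point holds conditionally. If it is taken over all participants, it counts people never at or above 10, some 41 to 69 % of PHQ-9 remitters under the same assumptions. It then overstates absolute descriptive rates in both arms.

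The primary RAS-r analysis and the secondary ANCOVAs on PHQ-9 and GAD-7 scores use neither definition and are unaffected. This is a cheap improvement, not a threat to the trial's main conclusions.

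**What to change.** **Response.** Define it separately for each scale, among participants at or above 10 on that scale at baseline, and fit two models: PHQ-9 responders and GAD-7 responders. If a single variable is preferred, require at least a 50 % reduction on a scale that was at or above 10 at baseline, and say that either one suffices when both were. Do not choose the scale by the higher raw score: PHQ-9 has nine items and GAD-7 seven, so their totals are not on the same range and the choice would tend to fall on PHQ-9.

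**Remission.** Report it per scale, only among participants at or above 10 on that scale at baseline, and state that denominator.

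**Cost.** Two sentences of wording, with no new data and no change to trial conduct. Denominators become smaller. Under the assumptions above, about 72 % of participants start at or above 10 on PHQ-9 and about 61 % on GAD-7, against about 80 % on at least one. The two models would thus use roughly 72/80 = 90 % and 61/80 = 76 % of the present subset.
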